#### Visits and data collection

##### Before intervention (T0)

Questionnaires assessing baseline children characteristics are sent to teachers and returned to principal investigators by e-mail. Evaluators visit each school to observe children and administer tasks. Visits take approximately 3 school days for a maximum of 12 children examined in each classroom. Questionnaires assessing teacher characteristics are sent to all teachers by e-mail at the beginning of the year.

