### Recruitment {15}

Teachers (pre-K level) were recruited between April and June 2021. Information about the study was distributed to public school principals and teachers through the departmental direction of education services (*Direction des services départementaux de l'Éducation nationale* (DSDEN)) using emails. Oral presentations of the study were then organized within each municipality. Interested teachers contacted the principal investigator (TV) of the study through emails and were accepted until sample completion.

Children were recruited in each classroom by the teachers, who transmitted information to parents regarding the study and collected consent to participate. As we targeted a final number of 10 observed students per classroom, a sample of 12 students was targeted in each classroom for the experimental and observational part of the protocol, to take into account the fact that recruitment in classrooms with a mixture of children from Pre-K and kindergarten levels may be reduced. Teachers provided one of the investigators in charge [OC] with a list of students fitting the inclusion and exclusion criteria. The principal investigator then randomly selected 12 children from that list and added two children who were put on a waiting-list, in case one of the 12 children initially targeted would be missing on the experimental visit day. Questionnaire data was collected for all children including children on the waiting-list. In order to also collect data on children with severe behavior problems who had to be excluded from the experimental and observation protocol (*specific exclusion criteria*), questionnaire data on two more children with severe behavior problems fulfilling the other inclusion criteria were collected in each classroom whenever possible.

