Description of the tools used and variables retained:School performanceIndicators of school performance are obtained 2 years after the beginning of the intervention, based on national evaluations taking place in the first and second years of primary school in France (*EVALAIDE* in Grade 1 and Grade 2). These evaluations target various literacy and math skills: reading out loud words, reading out loud text, understanding phrases while reading them, writing syllables, writing words, operating phonemes, recognizing letters, comparing letters, knowing letters’ names and sounds, understanding words, understanding phrases, understanding texts, reading numbers, writing numbers, visualizing numbers, comparing numbers, ordering numbers in sequence, resolving math problems, calculating mentally, adding numbers, subtracting numbers, and reproducing geometrical forms. *Mathematic skills, Reading skills*: based on these tests, we will create two outcomes corresponding to mathematics and reading skills.Standardized observations*Individualized Classroom Assessment Scoring System (InCLASS):* The InCLASS is a standardized naturalistic observation tool analyzing 3 to 5 years old children’s interactions in a classroom context [34]. It comprises 10 dimensions: (1) positive engagement with the teacher (which comprises the following indicators: attunement to the teacher, proximity seeking, and shared positive affect with teacher), (2) communication with the teacher (conversation initiated and maintained with the teacher, and variety of speech with the teacher), (3) teacher conflict (aggression, negative affect, attention-seeking behaviors, and non-compliance toward the teacher), (4) peer sociability (proximity seeking, shared positive affect, cooperation toward peers, and popularity), (5) peer communication (conversation initiated and maintained with peers, and variety of speech with peers), (6) peer assertiveness (positive initiation of interactions with peers and leadership toward peers), (7) peer conflict (aggression, negative affect, attention-seeking and confrontation toward peers), (8) engagement with tasks (sustained attention and active engagement in classroom activities), (9) self-reliance (personal initiative and independence in classroom activities), and (10) behavior control (patience, activity level matching expectations, and physical awareness) [13]. These dimensions have been grouped into four domains in a previous study using confirmatory factor analyses [13]: positive engagement with teachers (grouping positive engagement and communication with teacher), positive engagement with peers (peer sociability, peer communication, and peer assertiveness), positive engagement with tasks (engagement with tasks and self-reliance), and negative classroom engagement (teacher conflict, peer conflict, and the reversed score of behavior control). This tool has demonstrated solid inter-rater reliability, construct validity, and criterion validity [34]. *Positive engagement with teachers score, Positive engagement with peers score, Positive engagement with tasks score, Negative classroom engagement score:* Each dimension is rated on a 7-point scale, with higher score indicating higher frequency and/or quality of behavior within a dimension. Data from each of the observation cycles—collected by each data collector—are averaged to obtain final dimension scores. Mean score for the four domains are then calculated by averaging final dimensions scores within each of the four domains. Inter-rater agreement is calculated based on 12.5% of all observations, where the two data collectors independently observe the same child.Tasks*Challenging Situations task (CST):* An app-version of the full CST task is used to assess children’s emotional response in challenging interpersonal problems and ability to solve interpersonal problems [28]). Situation, emotion vignettes, and behavioral response vignettes are displayed on a tablet and responses are automatically registered. Emotional responses are composed of four different choices: happy, indifferent (“just ok”), sad, and angry. Behavioral responses are composed of four types of choices: a prosocial choice, an aggressive choice, an avoidant choice, and a dysregulated (“crying”) choice [27]. Examiners describe each situation picture and ask what the child would do in such a situation, by presenting response picture choices and asking the child to point at the picture corresponding to their emotion/behavior when/if the situation happens. Previous studies suggested that choosing sad emotion and prosocial behaviors on the CST constitutes adaptive behaviors that are linked with emotion knowledge and peer acceptance [28], and predicts classroom adjustment, pre-academic literacy skills, kindergarten readiness and academic achievement [26, 27, 81]. On the opposite, choosing aggressive response is associated with poor peer acceptance [28], poor classroom adjustment, and poor academic readiness [27]. *Adaptive responses score, Aggressive behavior score:* Along with previous studies [26, 81], the proportion of adaptive responses (Sad emotion + Prosocial behavior” responses) and aggressive behavior responses across the six vignettes (ranging from 0 to 6) are calculated.*Emotion matching task-expressive knowledge:* The expressive knowledge sub-task of the Emotional Matching Task (EMT) measures 3 to 6- years-old children expressive emotion knowledge – i.e., the ability to recognize and label expressions of others’ emotions (based on Izard test [46, 55];). A sample of 12 colored photographs representing ethnically-diverse children with emotional facial expression are presented on a tablet screen: happiness, sadness, fear/surprise, anger, and mixed (anger/sadness). Children are asked each time what the child on the picture is feeling [55]. The EMT has demonstrated good criterion validity, strong reliability and construct validity [55], and preliminary evidence for cross-cultural validity has been found [3]. *Expressive emotional knowledge score:* Each child verbal responses are assigned to a score of 0 (= incorrect response), 1 (=accepted response), or 2 (=correct response). Accepted verbal responses are pre-determined and listed in a table before test sessions using the instruction manual. All items are summed to obtain the total score, with higher score indicating better expressive emotion knowledge.*Executive functioning battery:* We use an app-version of the EF battery (“*EF Touch*”), a battery of six EF tasks designed for preschool children from 3 to 5 years, which was found to show good criterion validity [83]. Each response is automatically registered on a computer communicating with the tablet. Analyses of dimensionality show that performance on EF tasks is best characterized by a single EF factor [83]. The Houses, Pick the Picture and Something the Same tasks, when combined, best approximate an EF latent variable underlying performance on all the six tasks [84]. We therefore selected these three tasks to assess children’s EF within a single EF latent factor model. Finally, following the suggestion of Willoughby et al. [84], only two randomly selected tasks out of three are administered to each child using a planned missing design, in order not to overload attention capacities of children and to reduce global test burden. Score for the missing parameter is estimated through an imputation procedure.*Houses game (also named Working Memory Span game):* This task assesses working memory span. Children are presented with houses in which are located a line-drawing animal and a color dot. They are asked to name both the animals and the colors in each of the houses. Then, animals and color dots disappear from houses. Children have to recall either which animal *or* which color was in the target house, thus holding in mind two pieces of information and activating one of them (i.e., animal name) while overcoming interferences from the other (i.e., color name) [84]. Task becomes increasingly difficult as the number of houses on the screen increases (from one to three houses).*Pick the Picture (PTP) game:* This is a self-ordered pointing task assessing working memory. In this task, children are asked to touch once each picture appearing on the screen, so that all of the pictures “get a turn” [84]. Between each touch, location of pictures is changed in a randomized order. Difficulty of the task increases as the number of pictures increases (from two to six pictures).*Something’s the Same (STS) game:* This task evaluates cognitive flexibility. For each item, children are asked to shift their attention from one dimension of similarity to another dimension of similarity [84]. Initially, they are presented with two pictures that share one dimension of similarity (e.g., color, shape, size, etc.). Then, a third picture is presented, and children have to tell how this new picture is similar to one of the original pictures. This last picture always shares a different dimension of similarity with one of the original pictures. In the second part of the game, all pictures are presented at once and children have to identify two different dimensions of similarity.*Working memory span score 1 (Houses), Working memory span score 2 (Pick the picture), Cognitive Flexibility Score*: for each EF battery game, each response is coded into a dichotomous variable (0 = incorrect response, 1 = correct response). The total score is a proportion ranging from 0 to 1, with 0 indicating no items correct and 1 indicating all items are correct.*Peer acceptance task:* The peer acceptance task measures how a particular child is accepted and liked by his peers in his/her class. It is a peer rating measure inspired by Asher et al. (1979) sociometric procedure [14]. Children are presented with photos of their classmates. After identifying classmates on these photos, they are asked to sort each photo of classmates into three envelopes: happy smiley for “I really like to play with this child”; neutral smiley for “I kind of like to play with this child”; unhappy smiley for “I don’t like to play with this child”. Answers are coded 3, 2, and 1 respectively. This procedure shows adequate reliability and validity [14]. *Peer acceptance score*: After testing each child, we assess how many times a child photo is put in each envelope: a mean score is calculated by summing up the score on each trial and dividing by the number of children in the classroom minus one. The final score indicates how much a child is accepted by his peers, with higher scores indicating higher levels of acceptance.*Sharing task:* This task evaluates child sharing. The sharing task used in this study is a sub-section of the task designed by Flook et al. [38], divided into two trials. For each trial, children are presented with 10 stickers. They are told that they can keep as many stickers as they want for themselves and share as many as they want with another child. They then separate stickers between two different envelopes (identified with the photo of the assessed child and the photo of the other child). In the first trial, the other child is the one identified by the assessed child as his/her most-liked classmate, and in the second trial, the other child is the one identified as the least-liked classmate. Sharing ability has been shown to differ between groups that received an SEL intervention compared to control group [38]. *Sharing proneness score*: 20 minus the total number of stickers (ranging from 0 to 20) put in the “me” envelope across the two trials is calculated. Higher scores indicate higher levels of sharing tendencies.Teacher-rated questionnaires*Commitment to implement:* Teachers in the intervention group are asked about their commitment to implement the program using a single item: “I feel motivated to use the program/strategies in my classroom”. Previous study indicates that this item is a valid indicator of teacher commitment to implement various evidence-based programs, regarding construct validity and convergent validity with other measures of commitment and with commitment predictors [22]. Teachers in the intervention group are also asked whether they liked the training, whether they found it useful, whether they found the content of the program useful, whether they liked the content of the program, and whether their students liked the content of the program. These items are rated on a 5-point Likert scale (from 1= “strongly disagree” to 5 = “strongly agree”). *Commitment score*: We will construct a standardized commitment score based on these previous items. Higher score indicates higher commitment to implement. As the psychometric properties of this score have not been validated, we will check the internal validity of the constructed score using Cronbach’s Alpha.*Preschool and kindergarten behavior scale (PKBS)- Social skills:* The PKBS social skills [54] is a teacher-rated scale assessing preschool and kindergarten children’s social skills. The French version of the scale is divided into 5 subscales [20]: The first subscale, “social interaction’ consists of 10 items that reflect behaviors and attitudes necessary to develop and maintain good relationships and friendship with others (such as defend others’ rights, helping others), “participates in classroom or family discussions,” “shows affection for other children,” or “tries to understand another child’s behavior.” The second subscale consists of six items and reflects components of “agreeableness with peers,” such as “plays with several different children,” “makes friend easily,” or “smiles and laughs with other children.” The third subscale, “compliance,” relates to respect for adult authority and social norms, such as “follows instructions from adults,” “follows rules,” or “uses free time in an acceptable way.” The fourth subscale, “cooperation with peers,” describes behaviors such as “shares toys and other belongings” or “gives in or compromises with peers when appropriate.” Finally, the fifth factor, labeled “autonomy,” is composed of items such as “works or plays independently,” “adapts well to different environments,” or “attempts new tasks before asking for help.” *Total PKBS Social Skills Score, PKBS Social interaction score, PKBS Agreeableness with peers score, PKBS Compliance score, PKBS Cooperation with peers scores, PKBS Autonomy score; PKBS functional level categorical score*: The 34 items are rated on a 4-point Likert scale ranging from 0 (= Never) to 3 (= Often). Total raw scores and raw scores for each subscale are calculated by adding scores of each item, with higher scores indicating better social skills. For 5–6-year-old children, total raw scores are divided into 4 functional level categories based on child age: “high functioning” (scores 95 to 102), “average” (scores 76 to 94), “moderate deficit” (scores 59 to 75), and “significant deficit” (scores 0 to 58) to compute a functional level categorical variable.*Strengths and difficulties questionnaire (SDQ)-extended teacher version*: The SDQ-extended teacher version is a scale used to measure children’s externalized symptoms, internalized symptoms, and pro-social behaviors [42]. It is divided into five factors of five items each: emotional symptoms, conduct problems, hyperactivity-inattention, peer problems, and prosocial behavior. At the end of the questionnaire, 4 items explore impacts of difficulties (overall distress, social impairment, learning impairment, and burden for teacher and classroom) [41]. The SDQ displays satisfactory reliability and validity [42] and although its factor structure in French language remains uncertain [15, 16], the SDQ French version shows satisfactory reliability and content validity for the total difficulties score [16]. *SDQ total difficulties score, SDQ impact score*: The 25 items are statements rated on a 3-point Likert scale indicating to what extent each statement applies to a target child, with 0 = Not true, 1 = Somewhat true, 2 = Certainly true. All factors except Prosocial behavior are summed in a Total difficulties score. Items relative to impact of difficulties are coded from 0 to 2, with 0 corresponding to no impact or little impact, 1 corresponding to “Somewhat impactful”, and 2 to “Very impactful”. An impact total score ranging from 0 to 8 is then generated by summing these items. Higher scores indicate higher levels of difficulties and higher level of impact.*Student-teacher relationship scale-short form (STRS):* The STRS-short form is a teacher-rated scale exploring teachers’ perspective on their relationship with a designed child in their classroom [60]. The scale comprises two distinct factors, one measuring the degree to which teacher-child relationship is characterized by warmth, positive emotions and open communication (closeness), and the other measuring the degree to which the relationship is characterized by negative emotions and interactions (conflict). This scale possesses excellent psychometric properties across multiple samples [60]. The validation of the French version is ongoing [21]. *STRS Closeness score, STRS Conflict score:* The 15 items (8 items assessing Closeness, 7 items assessing Conflict) are scored using a 5-point Likert scale ranging from 1 (= Definitely does not apply) to 5 (= definitely applies). Total scores are then calculated for each factor.Teacher personal well-being P-WB:*Comprehensive inventory of mindfulness experience (CHIME):* The Comprehensive Inventory of Mindfulness Experience (CHIME) is a self-report multidimensional scale measuring “dispositional” (or “trait”) mindfulness in adults with or without knowledge or previous contact with mindfulness [9, 53]. It captures the following eight dimensions of “trait” mindfulness: awareness of internal experience, awareness of external experience, acting aware, self-acceptance and non-judgment, non-reactivity, openness and non-avoidance, ability to relativize, and insight. The CHIME exhibited good reliability and satisfactory construct validity [9]. The validated French version of the scale used in this study showed highly satisfactory psychometric properties as well [71]. *CHIME Total score:* The 37 items are rated on a 6-point Likert scale (from 1 = “fully applies” to 6 “does not apply at all”). Total score is calculated by inverting each item score and adding all inverted score. Higher scores indicate higher proneness to experience mindfulness in everyday life.*Warwick-Edinburgh mental well-being scale (WEMWBS):* The Warwick-Edinburgh mental well-being scale (WEMWBS) is self-report single-factor measure composed of positively worded items related to positive mental health and well-being [74]. It covers a wide-range of concepts associated with positive mental health, including hedonic and eudemonic well-being, satisfying personal relationship, and positive functioning. The original version displayed good content validity and reliability [74], and the French version used in this study showed good internal consistency, stability and construct validity [77]. *WEMWBS Total score*: The 14 items are rated on a 5-point Likert scale (from 1= “never” to 5 = “always”), with high score indicating higher mental well-being.*Satisfaction with professional life scale (Echelle de Satisfaction de Vie Professionnelle; ESVP):* The ESVP scale is a unidimensional French short self-report measure of general professional life satisfaction derived from the Satisfaction with Life scale from Diener et al. (1985) [29, 39]. It displays adequate level of internal consistency and temporal stability, and good construct validity [39]. *ESVP total score*: The 5 items are rated on a 7-point Likert scale (from 1= “strongly disagree” to 7 = “strongly agree”), with higher scores indicating higher professional life satisfaction.

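### The peer acceptance score divides ratings from at most 12 tested children by class size minus one, so this primary outcome is the mean rating multiplied by a class-level nuisance factor

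*Protocol article*

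**What the plan says.** The tools description in {18a} defines the task and its score. Each tested child looks at photographs of classmates, and "they are asked to sort each photo of classmates into three envelopes". "Answers are coded 3, 2, and 1 respectively" A child's score is called a mean and is found by "summing up the score on each trial and dividing by the number of children in the classroom minus one". The stated interpretation is: "The final score indicates how much a child is accepted by his peers, with higher scores indicating higher levels of acceptance".

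Other sections fix who gives ratings. Before intervention (T0): "Visits take approximately 3 school days for a maximum of 12 children examined in each classroom". Recruitment {15}: the investigator "randomly selected 12 children from that list and added two children who were put on a waiting-list", and the working target is lower still: "As we targeted a final number of 10 observed students per classroom". The same section adds up to two children per class with severe behaviour problems, who supply questionnaire data only. Trial design {8} reports that 28 of the 64 classes also contain kindergarten pupils, who do not meet the inclusion criterion in {10}.

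The first outcomes table in {12} lists the score as a primary Connection variable. Section {20a} places outcomes in weighted family indices and allows the baseline value as a covariate only when judged necessary.

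**The concern.** Class size minus one is the right divisor only if every classmate rates. Here the numerator holds ratings from the tested subset, while the divisor counts the whole class. The result is not a mean on the 1 to 3 scale. It shrinks as the class gets larger and as fewer children are tested, whatever the children think of each other.

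The distortion is shared by all tested children in a class, so it enters as between-class variance. That is the component a cluster trial can least afford: Sample size {14} takes ICCs below 0.1 for behavioural tasks and aims at an MDES of 0.35 SD. The distortion would also pass into any family index that contains the score. And if the number of children tested changes between visits, the scores of all tested classmates move together with no change in acceptance.

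**Working it through.** **Algebra.** Let R be the number of tested children in a class and C the class size. A tested child is rated by R − 1 others. If the true mean of those ratings is m, the sum is m(R − 1) and

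planned score = m × (R − 1)/(C − 1).

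The factor is 1 only when R = C.

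**With the protocol's own counts.** A class that fills every place described in {15} has at least 12 + 2 + 2 = 16 children.

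- R = 12: factor 11/15 = 0.73; possible range 0.73 to 2.20; a child rated 2 by everyone scores 2 × 11/15 = 1.47.
- R = 10: factor 9/15 = 0.60; possible range 0.60 to 1.80; the same child scores 2 × 9/15 = 1.20.

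The fall from 1.47 to 1.20 is 18%, with no change in acceptance.

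**With assumed larger classes** (the protocol states no class size). For C = 20, 25 and 30 the factor is 0.58, 0.46 and 0.38 with 12 raters, and 0.47, 0.38 and 0.31 with 10.

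**Effect on ICC and precision.** Simulation of 4,000 classes per setting. Assumptions: ratings rounded to 1–3 around a mean of 2.2, child SD 0.35, rater SD 0.7, latent class ICC 0.05. The unadjusted MDES is for 64 classes of 10, two-sided 5% and 80% power (both assumed):

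MDES = 2.80 × √[(4/64) × (ICC + (1 − ICC)/10)].

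| Assumed class size | Raters | Variance due to the factor | ICC, planned score | MDES, planned score |
|---|---|---|---|---|
| 22 | 12 | 0% | 0.04 | 0.26 |
| 22–26 | 12 | 13% | 0.16 | 0.35 |
| 20–28 | 10–12 | 41% | 0.44 | 0.49 |
| 18–28 | 8–12 | 62% | 0.63 | 0.57 |
| 15–30 | 8–12 | 71% | 0.72 | 0.61 |

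For the true mean rating, the ICC is 0.03 to 0.04 and the MDES 0.25 to 0.26 in every row. Worked example for the last row: 2.80 × √[0.0625 × (0.722 + 0.278/10)] = 0.61.

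**With baseline adjustment.** A separate simulation used classes of 20–28, child SD 0.3 and class SD 0.08. With 12 raters at both visits, the adjusted MDES was about 0.17 for either score, so nothing is lost. With raters varying independently between 10 and 12 at each visit, it was about 0.37 for the planned score and about 0.18 for the true mean.

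**The case against.** Several counter-arguments carry weight.

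*The classroom may mean the tested group.* On that reading 12 raters give a divisor of 11 and the formula works. The article does not define the term that way, and its plain meaning is the class. Loose wording in a condensed article is possible, but then the wording still needs correcting.

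*The score still measures acceptance.* This stands. A reader might infer that the outcome captures class size instead of acceptance. The text does not support that: within a class, tested children with the same number of raters keep their order exactly, and the factor's share of total variance could be anywhere from 0% to 71% in the settings tried.

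*Randomisation protects the comparison.* This stands for class size. Allocation was 1:1 within classroom type, so class size is balanced in expectation, and clustered standard errors cover chance imbalance. A reader might also infer a built-in false treatment effect. One tested child fewer per class in one arm would produce a spurious difference of about 0.5 SD under the 20–28 class-size assumption, but nothing in the protocol predicts such a difference. Both arms have the same target of 12, and two waiting-list children stand by for absences.

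*Baseline adjustment repairs it.* Partly. It removes the component that is stable between visits. It cannot remove changes in rater numbers, and {20a} leaves it optional.

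**Conclusion.** The concern holds in a limited form. As written, the divisor does not match the raters, and the score is the true mean rating times (R − 1)/(C − 1). That follows from the protocol's text without any assumption about class size, other than that classes contain children who are not tested, which {15} and {8} imply.

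The consequence is chiefly a higher ICC and lost precision for one of 15 primary variables, plus spurious movement between T0, T1 and T3 whenever rater numbers change. Bias between arms arises only if rater numbers differ by arm.

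How large the loss is cannot be settled from the protocol, because the spread of class sizes and rater numbers is not given. Under the assumed ranges the unadjusted MDES goes from no loss (0.26 SD), through the trial's own target of 0.35, to 0.61 SD.

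**What to change.** In {18a}, replace the divisor: the score is the sum of ratings a child received divided by the number of ratings that child actually received. Apply the same rule at T0, T1 and T3, and add a sentence saying who rates and whose photographs are shown. The factor is then 1 for any class size or number of raters, and the score is a true mean between 1 and 3. A minimum number of raters below which the score is set to missing would be a sensible but optional addition.

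The cost is one line in the protocol and one in the scoring code. Section {18a} already counts how often each photograph lands in each envelope, so no new data are needed. Trial status says analysis will not begin before the protocol is published, so the change can be made without knowledge of results.
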